# Enhancing Cognitive Functions in Older Adults With Mild Cognitive Impairment via Virtual Sail 3D: Protocol for a Feasibility Randomized Controlled Trial

**DOI:** 10.2196/85089

**Published:** 2026-01-15

**Keywords:** aging, cognitive functions, emerging technologies, feasibility, mild cognitive impairment, Sail, virtual reality

## Abstract

**Background:**

Innovative approaches, such as virtual reality (VR)–based cognitive rehabilitation, are becoming essential to healthy aging.

**Objective:**

This study aims to evaluate the feasibility and generate preliminary evidence regarding the effectiveness of an immersive VR-based cognitive remediation intervention for older individuals with mild cognitive impairment (MCI).

**Methods:**

A total of 40 individuals aged 65 years and older, of both genders with MCI, will be recruited and randomly assigned to the experimental or control group. The experimental group will participate in a 6-week VR-based cognitive remediation program, while the control group will receive healthy lifestyle education. Feasibility will be assessed through measures, including dropout rates, side effects, and satisfaction with the program. Preliminary effectiveness will be evaluated using assessments of cognitive functions, quality of life, functional mobility, depression and anxiety symptoms, regulation of social and biological rhythms, body awareness, and physical activity levels.

**Results:**

Recruitment began in May 2024 and is expected to conclude by November 2025; to date, 153 participants have been recruited and screened, with 39 enrolled. Preliminary analyses are planned for January 2026 and follow-up analyses for January 2027.

**Conclusions:**

This trial will provide insights into the feasibility and preliminary effectiveness of a VR-based intervention for older adults with MCI, with implications for its integration into preventive and rehabilitative care.

**Trial Registration:**

ClinicalTrial.gov NCT06579378; https://clinicaltrials.gov/search?term=NCT06579378

**International Registered Report Identifier (IRRID):**

DERR1-10.2196/85089

## Introduction

With the ongoing global increase in life expectancy, mild cognitive impairment (MCI) and dementia have emerged as leading causes of disability, especially among older adults [1]. Italy has the highest proportion of older adults in Europe, with 23% of its population aged 65 years and older [2]. Projections suggest that by 2050, 1 in 5 Italians will be in advanced age [2]. This demographic shift is expected to result in a shrinking working-age population, accompanied by a significant increase in both direct and indirect health care and social costs associated with age-related health issues [3]. MCI is characterized as a transitional phase bridging the gap between typical cognitive decline and the early stages of dementia [4]. Cognitive decline is frequently associated with symptoms of depression and anxiety, both of which contribute to a progressive deterioration in functional capacity during daily activities [5]. These conditions negatively impact quality of life (QoL) and disrupt the regulation of biological and social rhythms [6]. Given these considerations, both researchers and the European Union have increasingly focused attention on the critical objective of advancing research in the field of healthy aging, particularly in the development and implementation of nonpharmacological interventions aimed at preventing or delaying cognitive decline [7,8].

Emerging evidence from recent literature reviews highlights the beneficial impact of cognitive training, cognitive remediation interventions, and physical activity on cognitive performance in older adults, especially when these approaches are embedded within a comprehensive public health framework [9-11]. Research on active aging has been identified as a priority, particularly concerning the feasibility and effectiveness of nonpharmacological interventions aimed at preventing and/or delaying cognitive decline [11-13]. Risk factors such as physical, cognitive, and social inactivity are estimated to account for about 40% of the risk of developing dementia in a lifetime [14]. Contemporary reviews have shown that cognitive remediation interventions are effective in improving cognitive performance in older adults with and without cognitive decline [15,16]. Furthermore, cognitive remediation is a behavior-based training intervention aimed at improving cognitive functions (memory, attention, executive functions, social cognition, and metacognition) to achieve lasting results and their generalization [17]. There is substantial evidence supporting the effectiveness of such interventions in neuropsychological disorders, such as dementia, MCI, and behavioral disorders [18].

In recent years, there has been an increase in the use of immersive virtual reality (VR) software in clinical and rehabilitative settings as tools for rehabilitation and the improvement of various skills [18,19]. To date, there are few studies where immersive VR is used to enhance cognitive functions related to personal and social functioning, especially to prevent cognitive decline in older adults (aged 65 years and older), and the quality of evidence is rated as moderate to low [20,21]. VR serves as a core tool in facilitating cognitive and functional skill acquisition or enhancement, owing to its capacity to deliver immersive, ecologically valid, and highly realistic experiential learning environments [22]. These findings highlight not only improvements in specific cognitive domains, such as memory, language, and executive functioning, but also improvements in overall clinical, personal, and social functioning [20,21,23]. Despite the encouraging evidence, the methodological rigor of existing studies remains limited. Many studies lack comprehensive descriptions of the VR interventions and the specific methods used during the sessions. Additionally, most studies do not clarify the framework used to develop the interventions, which is essential for understanding the alignment between the hypotheses, outcomes, methods, and the VR programs designed to target specific cognitive domains. This lack of detailed information prevents the establishment of a standard operating procedure, which is crucial for ensuring the reproducibility of the intervention and for guiding the development of a future gold standard in the field [20,21,23-27]. Moreover, an integrative, multidisciplinary approach, grounded in individualized recovery-oriented objectives, is imperative for addressing the multifaceted and evolving needs of people with MCI.

The trial aims to assess the feasibility (primary outcome) of a 6-week intervention to improve cognitive functions using the immersive VR software “CEREBRUM” (Cerebrum VR Society) with sailing scenarios among the older adults with MCI. It also aims to evaluate, through a randomized controlled trial (RCT) design, the effectiveness of the experimental intervention in enhancing cognitive functions and/or mitigating further cognitive decline and deterioration (secondary outcome). Finally, it will verify whether the experimental intervention has a positive impact on (1) QoL, (2) functional mobility, (3) depressive and anxiety symptoms, (4) social and biological rhythms, (5) body awareness, and (6) physical activity levels (tertiary outcomes).

## Methods

### Study Design

This study is designed as a feasibility RCT. Assessments will be conducted at the following time points: T0 (0 weeks - baseline), T1 (6 weeks), T2 (12 weeks from T1), T3 (24 weeks from T1), T4 (36 weeks from T1), T5 (48 weeks from T1). The study adopted a longitudinal, 2-arm design, with participants randomized to either an active interventional protocol based on the Virtual Sail 3D (VSail) experimental protocol or to a control setting, “WEB-Health” (education on healthy lifestyles to promote active aging). Participants will be independently randomized in a 1:1 ratio to one of the two parallel assignment groups: (1) VSail or (2) WEB-Health. The study protocol is written according to the CONSORT (Consolidated Standards of Reporting Trials) 2010 statement for randomized pilot and feasibility studies [28] (Figure 1).

**Figure 1 figure1:**
[figure not shown]
CONSORT flow diagram.

### Participants, Recruitment, and Setting

The target population includes older participants with MCI conditions.

Inclusion criteria are being 65 years and older of both genders, without conditions that would prevent them from participating in the activities of the experimental intervention “VSail,” without severe issues with autonomous mobility, with MCI according to Addenbrooke’s Cognitive Examination-Revised (ACE-R) for cognitive functions, which also includes the Mini-Mental State Examination (MMSE) [29], with the following ranges: ACE=66.93-84.93 and/or MMSE=27.02-27.11, and signing the informed consent.

Exclusion criteria are severe cardiovascular conditions, severe issues with autonomous mobility, severe metabolic disorders not pharmacologically compensated, severe neurological conditions that prevent from participating in the experimental protocol, such as a stroke within the past 2 years, Parkinson disease, epilepsy, or dementia (Alzheimer, vascular, etc), severe ongoing bronchopulmonary disorders, severe ongoing renal disorders, glaucoma, retinal detachment, or other serious vision conditions that do not allow the safe use of VR technology, active malignant neoplasm that do not allow the hinders participation in the intervention.

Recruitment activities will be conducted at the sites of the project’s partner units, namely, the Consultation-Liaison Psychiatry and Psychosomatics Center, the Cardiology–CCU–Hemodynamics Unit, and the Multidisciplinary Sleep Medicine Center of the University Hospital of Cagliari (AOU Cagliari), Italy. At each site, infographics will be displayed and informational brochures about the project will be made available so that outpatients attending the relevant clinics can express their interest in participating. In addition, a health care professional will contact by telephone all patients who, based on the study’s inclusion and exclusion criteria, will be identified by clinicians of the partner units as potentially eligible. All patients who express interest and meet the eligibility criteria will then be invited to provide written informed consent and to undergo screening with the ACE-R [29].

Participants who screen positive for MCI will be enrolled and subsequently randomized to the experimental or control arm. Those who screen negative will be excluded from study participation.

According to the inclusion and exclusion criteria, recruitment will continue until the target sample size is reached, allowing for randomization and the conduct of interventions.

All assessment activities using the instruments specified in the protocol, as well as the implementation of both the control and experimental interventions, will take place at the Consultation-Liaison Psychiatry and Psychosomatics Center. These activities will be conducted by mental health professionals who will be duly trained in the use of the assessment tools and in the delivery of the VR-based cognitive remediation protocol (experimental intervention) and the web-based healthy lifestyle seminars (control intervention). Motor performance assessment (balance, gait, and functional mobility) will be carried out with the support of biomechanical engineers who will receive appropriate training for this purpose.

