### Randomization and Allocation Concealment

Participants who meet the eligibility criteria will be randomly assigned to one of the two groups: an intervention group and a control group. Randomization will be conducted after baseline assessment. Randomization will be computer-based and concealed. The individuals conducting the randomization procedure will be blinded to participants’ identities and statuses and will not receive any information about them. Participants will be randomly assigned to experimental or control groups in a 1:1 ratio using block randomization. Allocation codes were concealed.

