### Blinding

Due to the intervention method, it may not be feasible to effectively blind both the participants and professionals engaged in the study.

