### Outcomes

The primary outcomes regard feasibility and include (1) dropout rates, (2) the proportion of recruited participants among those considered eligible, (3) the incidence of potential adverse effects associated with the use of immersive VR technology (eg, nausea, dizziness, visual fatigue, and headache), and (4) the level of perceived satisfaction reported by participants following the experimental intervention.

The secondary outcomes regard cognitive functioning and include (1) executive functions, (2) memory, (3) visuospatial abilities, (4) selective attention, and (5) general cognitive functioning.

The tertiary outcomes regard psychosocial and physical functioning and include (1) QoL, (2) depressive symptoms, (3) anxiety symptoms, (4) regulation of social and biological rhythms, (5) body awareness, (6) levels of physical activity, and (7) mobility.

Also, the following sociodemographic and clinical variables will be collected for each participant: gender and age, marital status, educational attainment, past and current occupational status, history of and current organic physical illnesses, history of and current mental health diagnoses, and current medication use.

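### One pool of professionals delivers the interventions and assesses outcomes, no masked assessor is planned for the T1–T5 cognitive tests, and the reason given does not cover testers or scorers

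*Protocol article*

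**What the plan says.** Three parts of the Methods bear on this.

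- **Participants, Recruitment, and Setting.** The subject of the staffing paragraph is "All assessment activities using the instruments specified in the protocol, as well as the implementation of both the control and experimental interventions", all at one centre. The next sentence reads "These activities will be conducted by mental health professionals who will be duly trained in the use of the assessment tools" and continues "and in the delivery of the VR-based cognitive remediation protocol (experimental intervention) and the web-based healthy lifestyle seminars (control intervention"). One professional group therefore holds both roles, and no separation between them is stated. For balance, gait and mobility only, the work "will be carried out with the support of biomechanical engineers who will receive appropriate training for this purpose".
- **Blinding.** The whole section is one sentence. Citing the intervention method, it says that "it may not be feasible to effectively blind both the participants and professionals engaged in the study". Assessors are not treated separately from those who deliver the interventions.
- **Randomization and Allocation Concealment.** "Randomization will be conducted after baseline assessment". The only role described as blinded is the one running the allocation: "The individuals conducting the randomization procedure will be blinded to participants’ identities and statuses".

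The Outcomes section places cognition second to feasibility: "The secondary outcomes regard cognitive functioning and include (1) executive functions, (2) memory, (3) visuospatial abilities", followed by attention and general cognition. The Data Analysis section calls these analyses exploratory, and says that their effect sizes are wanted to choose and rank outcomes for a later, fully powered RCT.

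**The concern.** The nature of a VR programme prevents masking of the person wearing the headset and of the operator running the session. It does not by itself prevent masking of a different person who later gives a memory test or scores a drawing. The plan uses the first fact to cover both situations.

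Several of the cognitive measures depend on an examiner's prompting or scoring judgement. If that examiner knows the arm, and perhaps trained the participant, scores may drift towards the expected result. Labelling the analysis exploratory does not remove a systematic error, and no later analysis can separate it from a treatment effect. What is at stake is the use the plan makes of these estimates: an outcome that is easily influenced by the examiner could look more promising than one that is not, and be carried forward for that reason.

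**Working it through.** The document gives no figure to reproduce on this point: the sample of 40 rests on precedent, and the article says that no power calculation was made for effectiveness. The check is mainly a reading, with a small calculation for scale.

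**1. Who is masked, role by role**

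| Role | What the article says |
|---|---|
| Staff running the randomization | Blinded |
| Participants | Blinding may not be feasible, because of the intervention method |
| Professionals who deliver VSail or WEB-Health | Same statement |
| Professionals who test and score | Same pool, same statement; no separate reason |
| Engineers supporting motor tests | Masking not mentioned |

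The stated reason fits rows two and three. It does not reach row four.

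**2. Which visits are exposed**

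T0 precedes allocation, so arm knowledge cannot affect it. T1 to T5 follow allocation. With 40 participants, that is 40 × 5 = 200 planned participant-visits.

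**3. How bias would enter the planned contrast**

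Let *b*V and *b*C be the average examiner error at a follow-up visit in the VSail and control arms, with none at T0. The contrast in change from baseline is then the true effect plus (*b*V − *b*C). Error common to both arms cancels; differential error enters in full.

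A differential is plausible because contact differs by arm (Interventions section):

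- VSail: 12 sessions × 50–60 minutes = 600–720 minutes, with an operator who adjusts difficulty to the user and gives feedback.
- WEB-Health: 3 webinars × 50–60 minutes = 150–180 minutes, in plenary over Zoom.

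The Discussion also says that the team expects cognitive improvement with VSail. This makes a bias towards VSail the likelier direction, but it does not demonstrate one.

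**4. Scale, with the bias as an assumption**

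The inputs are 20 per arm (from the article), no true effect, and a differential bias *b* in SD units (assumed, since the documents give none).

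- SE of a standardised difference ≈ √(1/20 + 1/20) = √(2/20) = 0.316.
- 95% half-width ≈ 1.96 × 0.316 = 0.62 SD.
- Chance of nominal two-sided p < 0.05 = 1 − Φ(1.96 − *b*/SE) + Φ(−1.96 − *b*/SE).

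| Assumed *b* (SD) | *b*/SE | Chance of p < 0.05 with no true effect |
|---|---|---|
| 0 | 0 | 5.0% |
| 0.1 | 0.32 | 6.2% |
| 0.2 | 0.63 | 9.7% |
| 0.3 | 0.95 | 15.8% |

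Throughout this range the bias is smaller than the sampling error. Unlike sampling error, it would not shrink with more participants tested in the same way.

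**5. Whether the plan discloses it**

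The limitations in the Discussion (Principal Findings) cover recruitment, technological familiarity, the single centre and low power. Unmasked assessment is not among them.

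**The case against.** The strongest reply has five parts.

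- **The text is softer than it may sound.** The Blinding section says only that blinding may not be feasible. A reader might infer that operators will test their own participants. The article shows a shared pool with shared training, not that pairing, and a roster could sit in the full protocol. This stands as a limit on the claim. It does not answer the point, because the article has a blinding section and a staffing paragraph, and together they set out a shared pool with no masked assessor and a reason that does not fit assessors.
- **Masking may not be achievable.** A reader might infer that the present staff could certainly mask every assessment. The documents give no staff numbers or roster, and they name the engineers for motor tests only. The plural professionals makes separation plausible, no more. This stands.
- **The stakes are modest.** Dropout and recruitment are counts, and side effects and satisfaction are self-reported. None of them depends on masked cognitive scoring, and the cognitive analyses are declared hypothesis-generating. This stands, and it limits the weight of the point. A reader might go further and conclude that the next trial would be undersized by a definite factor. The documents do not say that it will be sized on the observed point estimate, so no such figure is supported.
- **Re-scoring is a partial remedy.** A masked scorer inherits the original TMT timing, and cannot see the behaviours rated in the FAB or how any test was prompted. This stands.
- **It is late.** By submission 39 of 40 were enrolled, and pre-post analyses were set for January 2026, so much T1 testing may be done. This stands for T1. T5 falls 48 weeks after T1, and follow-up analyses run to January 2027, so later visits of late enrolees can still be changed.

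**Conclusion.** The point holds in a limited form. As written, one pool of mental health professionals assesses outcomes and delivers both arms, no masked assessor is planned, and the reason offered does not extend to testers or scorers. T0 is protected. Examiner-administered or examiner-scored cognitive tests at T1–T5 are open to detection bias, plausibly towards VSail, in the effect sizes that are to guide outcome selection.

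The size is unknown. The range of 6.2% to 15.8% in place of 5% rests on an assumed differential bias of 0.1–0.3 SD, 20 analysed per arm, a single comparison and a normal approximation; it shows scale and estimates nothing. The primary feasibility outcomes are unaffected. This is an improvement worth making while visits remain, not a defect that undermines the trial's main purpose.

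**What to change.** 1. **Remaining T1–T5 visits.** State that no professional tests or scores a participant to whom they delivered VSail or WEB-Health, and allocate the existing professionals accordingly. Keep the tester unaware of arm where possible, and ask participants not to disclose it.
2. **Visits already done.** Have Rey Figure drawings, and other written responses where kept, re-scored under ID code by a colleague masked to arm and visit. The article does not say what has been kept, so check this first. Do not rely on re-scoring for TMT times or FAB ratings.
3. **Where neither is possible.** Report which assessments were unmasked, and add this to the limitations in the Discussion.
4. **Blinding section.** Separate participants, deliverers and assessors, and give each its own statement and reason.

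The cost is rota planning and some re-scoring time. If the existing professionals can be divided in this way, no added posts are needed, but the article does not give the numbers to confirm that. There are two downsides: less scheduling flexibility, and a possible change of assessor within participants between early and late visits. Recording the assessor's code at each visit would let that change be described.

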### Randomization and Allocation Concealment

Participants who meet the eligibility criteria will be randomly assigned to one of the two groups: an intervention group and a control group. Randomization will be conducted after baseline assessment. Randomization will be computer-based and concealed. The individuals conducting the randomization procedure will be blinded to participants’ identities and statuses and will not receive any information about them. Participants will be randomly assigned to experimental or control groups in a 1:1 ratio using block randomization. Allocation codes were concealed.

### Blinding

Due to the intervention method, it may not be feasible to effectively blind both the participants and professionals engaged in the study.

